### 3. STUDY DESIGN

**Design:** We will conduct a prospective, cluster-randomized trial. We aim to include 1830 newborns from 10 hospitals in the Netherlands during an 18-month period. Cluster-randomization happens at the hospital level. A cluster is finished when a total of 183 participants are included into the cluster. Once finished, a hospital cannot be randomized again. Participating hospitals provide care up to Level II special care for stable or moderately ill newborns, with annual birth rates between 1200 and 4000 births per year, and all use the Dutch national guidelines to guide antibiotic use in newborns at-risk for EOS.

This cluster randomized design can be used when randomization at individual level is difficult and/or creates possibility for bias. The cluster-randomized study design matches our study objectives perfectly because time for randomization is very restricted due to the immediate need to start antibiotic therapy in some newborns. Furthermore, the clustered approach prevents confusion and contamination between the different protocols being compared, thereby limiting bias. After randomization, the assigned protocol is considered standard care for newborns with suspected EOS within 0-24 hours after birth during the study period in that hospital. This means that the NVK guidelines or the EOS calculator (depending on randomization) will be used for all newborns at risk for EOS (within 0-24 hours after birth) in the particular hospital, independent of study participation. It is noteworthy that every attending physician always has the option to choose for clinical management according to another protocol instead of the assigned protocol.

Newborns who do not meet the inclusion criteria, and develop clinical symptoms (suspected for EOS) >24 hours after birth, the NVK guidelines will be used since the EOS calculator is only validated for use in the first 24 hours after birth. If newborns are eligible for inclusion and attending physicians opt for clinical management not according to the advice of the assigned study protocol, this will be recorded with deviations being noted with accompanying justification in both the electronic health record and the electronic Case Report Form (eCRF). After informed consent is obtained data will be collected and used for analysis, and follow-up data collection will ensue.

In order to meet requirements of the European Regulations for Medical Devices, the EOS calculator has been developed as a smartphone application specifically for this study, and CE marking has successfully been obtained (see chapter 5). Only in the five hospitals randomized for the EOS calculator this application will be available for all physicians who have a treatment relationship with newborns at risk for EOS.

**Equality:** We use the same strategy to include and observe participating newborns to ensure that the control group and the intervention group are equally recruited and monitored. Each newborn in participating hospitals is evaluated for elevated EOS risk. In case one or more criteria for elevated maternal EOS risk or neonatal clinical signs of EOS are met (in accordance with the NVK guideline, Table 1), clinical evaluation of the newborn by a pediatric resident or pediatrician will take place within 4 hours after birth. After concluding eligibility, the advice of either the NVK guideline or the EOS calculator (depending on randomization) to observe or to start antibiotic therapy is followed. We maintain an observation period of at least 12-24 hours for the NVK guideline-group and at least 24 hours for the EOS calculator-group. These observation periods are in accordance with the advice of both guidelines. Observation in both groups will consist of controls of vital parameters (heart rate, respiratory rate, and temperature) every 3 hours by the nurse, and a minimum of two physical examinations (within 4 hours after birth and before discharge) by the physician.

**Usual care NVK guideline (control group):** The NVK guidelines use eight maternal and fifteen neonatal risk factors, each categorized as either red flag or non-red flag (Table 1, see next page). These criteria guide clinicians on the management in case of suspected EOS. Briefly, antibiotic treatment is recommended in the presence of at least one red flag and, or, two or more non-red flags. Before the start of antibiotic treatment, the guidelines advise to take a blood culture, whereas a C-reactive protein (CRP) level can be considered. They advise to continue antibiotic treatment for at least 36-48 hours, which is based on the time to positivity of blood cultures. The guidelines advise to repeat a CRP after 24-36 hours after the start of antibiotic treatment. Discontinuation of antibiotic treatment after 36 hours can be considered in case of a negative blood culture and when the initial clinical suspicion of infection was not strong, the newborn's clinical condition is reassuring with no clinical indicators of possible infection, and CRP concentrations are repeatedly below <10 mg/L.

An observation period of at least 12 hours is recommended in the presence of one non-red flag (this could be a maternal risk factor or a clinical symptom of the neonate). For this study we maintain an observation period of at least 12-24 hours. Antibiotic treatment is recommended when an infection is suspected during this observation. Newborns will be discharged from the hospital if there are no maternal risk factors, and the newborn is in good clinical condition and the gestational age is more than 36 weeks. If the guidelines recommend an observation period, the newborn is discharged after repeating physical examination that conclude that the newborn is in good clinical condition. In case antibiotic treatment is started, discharge depends on the duration of treatment and the clinical course. At discharge,

parents/guardians receive information when to contact the hospital in case of signs of infection within the first 14 days of life.

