| Non-red flags                                                                                                                                                                                           |                                                                                                    |
| Invasive group B streptococcal infection in a previous neonate                                                                                                                                                 | Altered behavior, -responsiveness or -muscle tone                                                  |
| Maternal group B streptococcal colonization, bacteriuria or infection in the current pregnancy                                                                                                                 | Feeding difficulties (feed refusal, gastric retention, vomiting, distended abdomen)                |
| Suspected or confirmed rupture of membranes without contractions for more than 24 hours in a term birth                                                                                                        | Apnea and bradycardia                                                                              |
| Preterm birth following spontaneous labor (before 37 weeks' gestation)                                                                                                                                         | Signs of respiratory distress (tachypnea, moaning, retractions, nasal flaring)                     |
| Suspected or confirmed rupture of membranes for more than 18 hours in a preterm birth                                                                                                                          | Hypoxia (for example, central cyanosis or reduced oxygen saturation level)                         |
| Intrapartum fever higher than 38°C or suspected or confirmed chorioamnionitis                                                                                                                                  | Neonatal encephalopathy                                                                            |
|                                                                                                                                                                                                                | Need for cardio-pulmonary resuscitation                                                            |

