### 4.2 Inclusion criteria

In order to be eligible to participate in this study, a subject must meet all of the following criteria:

- postmenstrual age of 34 weeks or more;
- age between 0-24 hours;
- at least one EOS risk factor or clinical sign of infection (suspected of EOS) present within the first 24 hours of life (Table 1);
- parental/guardian consent.

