## **6.2 Randomization, blinding and treatment allocation**

Randomization will take place at cluster level for either the EOS calculator or control (antibiotics administration according to NVK directive usual care). Centers will be randomized as clusters using a computer-generated algorithm. After randomization, the hospital will also switch to the protocol assigned after randomization (NVK guideline or EOS calculator use). This assigned protocol is standard care for newborns with suspected EOS during the study period in that hospital. This is independent of participating in this study (see chapter 3). Thus, hospitals nor physicians are blinded for the assigned study protocol. However, physicians may always opt for clinical management not according to the assigned study protocol.

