## **6.3 Study procedures**

For all included newborns, maternal and neonatal data on risk factors will be collected. The newborn's date and time of birth will be collected because the most important collected parameters are time dependent and need these date and time of birth as a reference. Physical examinations of the newborn will be performed at least twice (at birth and before discharge), and more often if necessary (depending on clinical findings). Finally, for

participating newborns, a single (online) questionnaire will be sent (via Castor EDC) to the parents/guardians to fulfill on day 14 after birth. The questionnaire includes a minimum of 22 questions, which may expand up to 32 questions (since some questions are dependent of other questions). It will take about 10-15 minutes to complete.

For newborns without antibiotic therapy, clinical observation for at least 12-24 hours will be performed: vital parameters (heart rate, respiratory rate, and temperature) will be measured 1, 3, 6, 9, 12, 15, 18, 21 and 24 hours after birth. This is part of standard medical treatment. Data on physical examinations will be collected. Data on readmission for suspected or proven EOS will be collected.

For newborns with intravenous antibiotic therapy, two blood samples will be taken: during insertion of the intravenous cannula before starting antibiotics (blood culture; blood cell count, CRP), and approximately 24-36 hours after the start of antibiotics by capillary or vena puncture (CRP). This is part of standard medical treatment. Duration of hospital stay will be at least 24-36 hours, could be extended depending on the clinical condition and blood culture results and non-EOS factors. During admission the need for any kind of respiratory support and the need for intravascular fluid administration will be recorded daily. Referral to a neonatal intensive care unit (NICU) will be recorded and relevant clinical data during NICU admission will be obtained by the main investigator or the research nurse/assistant of the participating hospital. Data on sort and duration of antibiotic therapy and blood culture results will be collected.

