## 8. STATISTICAL ANALYSIS

### 8.1 Primary study parameters

The analyses will be performed according to the Intention-To-Treat and Per Protocol principle (as secondary analysis). The primary analysis will estimate the relative risk with 95% confidence intervals and p-values for the primary outcomes, using a generalized linear mixed model with log link and binomial distribution, with random intercepts and random slopes per cluster as appropriate. A significance level of 5% will be used.

Both superiority for the proportion of patients that started antibiotic therapy and non-inferiority for adverse clinical outcome must be shown to conclude the effectiveness of the EOS calculator. The use of EOS calculator will be considered superior when it leads to at least a 15% absolute reduction in the proportion of patients who started antibiotic therapy. We expect 10% neonatal complications in the control group. The use of the EOS calculator will be considered non-inferior when the upper bounds of a 95% confidence interval of the relative risk of complications does not exceed 1.5 (comparable to a 15% complication rate).

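### Allocation is known before eligibility is judged, and the entry list doubles as the control arm's treatment rule, so common criteria limit but cannot ensure equal recruitment

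*Protocol*

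**What the plan says.** - **The assurance.** Section 3 (Equality) states: "We use the same strategy to include and observe participating newborns to ensure that the control group and the intervention group are equally recruited".
- **Allocation is open and comes first.** Under section 6.2, hospitals are randomised and the assigned protocol becomes standard care: "Thus, hospitals nor physicians are blinded for the assigned study protocol".
- **Eligibility is judged inside an already assigned hospital.** Section 3 (Equality) has staff decide on eligibility first and then act on the advice of whichever strategy their hospital was allocated.
- **One item is enough for entry.** Section 4.2 requires "at least one EOS risk factor or clinical sign of infection (suspected of EOS) present within the first 24 hours of life", with reference to Table 1. Some Table 1 items are objective maternal facts. Others are bedside judgements, for example "Altered behavior, -responsiveness or -muscle tone", feeding difficulties, signs of respiratory distress and local signs of infection.
- **Table 1 is also the control arm's treatment rule.** Section 3 (Usual care): "antibiotic treatment is recommended in the presence of at least one red flag and, or, two or more non-red flags". A single non-red flag leads to observation. In calculator hospitals the advice comes from an algorithm that combines maternal factors with the physical examination.
- **Consent is deferred.** Section 9.2 allows it more than 24 hours after birth and collects nothing on those who refuse.
- **Primary model.** Section 8.1 specifies the analysis "using a generalized linear mixed model with log link and binomial distribution, with random intercepts and random slopes per cluster as appropriate".
- **Data available.** Section 6.3: "For all included newborns, maternal and neonatal data on risk factors will be collected".

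**The concern.** In a cluster trial, randomising hospitals balances, in expectation, the births that occur in them. It does not balance the newborns whom staff identify and enrol once they know the arm. Protection then depends on identification being independent of allocation. Section 3 rests that on a shared list, yet the list does different work in the two arms. In a control hospital, recording a further sign can change the recommended management through the flag count. In a calculator hospital the same entry opens eligibility, and the advice follows another route. Deferred consent gives a second opening, because the family may be approached after management is known.

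Both co-primary outcomes are proportions of enrolled, Table 1-positive newborns. Extra low-risk newborns in one arm lower that arm's antibiotic proportion and its complication proportion together. If they are in the calculator arm, both outcomes move in its favour, so requiring both to succeed gives no protection. If they are in the control arm, a real antibiotic reduction shrinks and non-inferiority becomes harder to show. Section 6.1.1 concedes that the open design may cause bias and relies on the cluster design and fairly objective criteria. That remark concerns the outcome criteria, and clustering does not guard against differential identification after allocation.

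**Working it through.** **Plan inputs (sections 4.1, 4.4 and 8.1).** 20% of births eligible; control antibiotic rate 40%; target 25%; safety composite 10% in both arms; margin 5 points (relative risk 1.5); ICC 0.0025; 10 hospitals; 164 analysed per hospital, so 820 per arm.

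**The plan's own figures.**
- Superiority: 40% v 25%, two-sided 5%, 80% power gives 152 per arm. With 33 per hospital, 152 × (1 + 32 × 0.0025) / 5 = 32.8, so 33 × 10 = 330. Reproduced.
- Non-inferiority: 10% v 10%, margin 5 points, one-sided 2.5% gives 566 per arm. The design effect at 164 is 1 + 163 × 0.0025 = 1.4075, and 2 × 566 × 1.4075 = 1593, within 3% of the stated 1640. Power at 164 per hospital is 81.2%. Reproduced closely enough to use these inputs.

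**Assumption, not in the protocol.** The calculator arm enrols a relative excess x of low-risk newborns. Their risk of each outcome is a fraction r of their arm's average: r = 0 (never treated, no events) or r = 0.5 (half the average).

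**Formulas.**
- Antibiotic rate with no true effect: 0.40 × (1 + r·x) / (1 + x).
- Apparent complication rate when the true rates are 15% v 10%: p1 = 0.15 × (1 + r·x) / (1 + x), with p0 = 0.10.
- SE(log RR) = √{1.4075 × [(1 − p1)/(820·p1) + (1 − p0)/(820·p0)]}.
- Chance that the upper 95% limit is below 1.5: Φ{[ln 1.5 − 1.96·SE − ln(p1/p0)] / SE}.

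| x | r | Spurious antibiotic reduction (points) | Apparent RR | Chance of declaring non-inferiority |
|---|---|---|---|---|
| 0 | – | 0 | 1.50 | 2.5% |
| 10% | 0 | 3.6 | 1.36 | 8.5% |
| 20% | 0 | 6.7 | 1.25 | 19.5% |
| 10% | 0.5 | 1.8 | 1.43 | 4.7% |
| 20% | 0.5 | 3.3 | 1.38 | 7.7% |

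Example row (x = 10%, r = 0): 0.40/1.10 = 36.4%, so 3.6 points; p1 = 0.15/1.10 = 0.136; SE = 0.162; Φ{(0.405 − 0.318 − 0.310)/0.162} = 0.085.

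**Scale of x.** If all of the excess came from flagging, x = 10% means flagging 22% of births instead of 20%, and x = 20% means 24%.

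**The 15-point criterion.** With r = 0, bias alone would need 0.40/(1 + x) = 0.25, that is x = 60%. Bias can, however, add to a smaller real effect: a true rate of 30% with x = 20% appears as 0.30/1.20 = 25%.

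**Reverse pattern.** With a true calculator rate of 25% and the excess in the control arm (r = 0), the control rate appears as 36.4% (x = 10%) or 33.3% (x = 20%). The true 15-point reduction then shows as 11.4 or 8.3 points.

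**Room for the second route.** 2000 births × 20% × 1.5 years = 600 eligible per hospital, of whom 183 (about 31%) are needed. Approach and consent can therefore dampen or enlarge any difference that arises at flagging.

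**The case against.** The strongest reply is that the risk is generic to open cluster trials, hypothetical in size and already mitigated. Every newborn is evaluated, flagged newborns are examined within 4 hours, all hospitals already use the Dutch guideline, the assigned protocol applies whether or not a family takes part, and many maternal items are objective. These points stand as mitigation. They do not make recruitment equal by construction, because a sign alone is enough for entry and whoever calls it knows the arm.

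Four stronger readings are tempting, and the protocol does not support them.

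- *That soft signs trigger treatment only in control hospitals.* One non-red flag leads to observation there, and the calculator also uses the physical examination. What differs by arm is the flag-count rule.
- *That under-calling signs in control hospitals favours the calculator on both outcomes.* If one of two non-red flags is dropped, the newborn stays eligible on the other and treatment is no longer recommended. The denominator is unchanged, the control antibiotic rate falls, and superiority becomes harder to show. Under-calling removes a newborn only if no Table 1 item is left.
- *That this bias could by itself produce the superiority finding.* No shift in the table reaches 15 points.
- *That the primary model is unadjusted.* Section 8.1 names link, distribution and random effects and does not list fixed effects. A statistical analysis plan that is not at hand may add covariates, so the silence is not counted as an error.

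**Conclusion.** The point holds as a structural weakness and an unsupported assurance, not as a demonstrated bias. Known allocation, entry on a single judgement-based sign, a list that doubles as one arm's treatment rule, and deferred consent without data on refusers together mean that a shared list cannot ensure equal recruitment.

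The illustrated range, about 2 to 7 points on antibiotics and about 5–20% instead of 2.5% for non-inferiority at the margin, rests on an assumed 10–20% excess in the calculator arm, extra newborns at zero to half the average risk, the plan's ICC and rates, and a normal approximation. The upper end needs extra newborns who are never treated and have no events, which is extreme for infants with a Table 1 item. The protocol does not say which direction to expect. The non-inferiority side matters more, because a modest difference in risk mix there noticeably raises the chance of a false reassurance on safety.

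**What to change.** **Section 8.1**
1. Adjust both co-primary models for gestational age and the maternal factors fixed by birth and already collected: duration of membrane rupture, GBS status and highest intrapartum temperature. Name a fallback, such as a modified Poisson model, in case the log-binomial model does not converge.
2. Prespecify the same analyses in newborns who qualify on a maternal Table 1 criterion documented by birth (for example spontaneous preterm birth, prolonged rupture, GBS, a previous infected neonate, or measured fever). Keep this as supporting evidence and not as a condition for the claim. Requiring agreement in direction is undefined for non-inferiority: if it meant a relative risk below 1, it would fail about half the time under the plan's equal 10% rates.
3. Report by arm the share who entered on neonatal signs only and the completeness of the maternal data. The maternal factors are calculator inputs, so their ascertainment may itself differ by arm.

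**Section 3 (Equality)**

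Replace the claim of ensuring equal recruitment with a statement that common criteria are used to limit differential recruitment.

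**Cost.** Wording and one extra analysis on data already collected, with no added patients or procedures. The maternal-criterion subset is smaller and less precise and still depends on who consents. Adjustment cannot remove differences in factors that are not measured.

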controls of vital parameters (heart rate, respiratory rate, and temperature every 3 hours) by the nurse. In case of routine controls, re-evaluation of physical appearance by a pediatric resident or pediatrician will take place within 24 hours postpartum. As an additional safety precaution in our study, the newborns will be observed for 24 hours using vital parameters. In case antibiotics are started, the need for further treatment is assessed after 24-36 hours of treatment depending on blood culture results, infection parameters, and clinical condition of the newborn. Discontinuation of antibiotics and discharge is at the discretion of the treating physician.

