#### 6.1.2 Secondary study parameters/endpoints

- The total duration of antibiotic therapy.
- The proportion of antibiotic therapy started for suspected and, or proven EOS if symptoms started between 24-72 hours after birth.

- Quality of life: To get an impression of the impact of (suspected) early-onset sepsis on the quality of life (QoL) of both parents/guardians and their child, parents/guardians will be asked to fill in a questionnaire on day 14 after birth. Our questionnaire is based on (parts of) two questionnaires, which were used in different studies assessing the effect of early intravenous-to-oral antibiotic switch (30), and the influence of resiliency and stress on parental/guardian perspective of the future QoL of their newborns (31). The first part collects information on medical factors after hospitalization (side effects, number of medical visits, readmission, and medication use) and basic needs of the newborn (sleep quality of the patient, (breast)feeding success rate). The second part addresses the subjective parental/guardian evaluation of the impact of newborns' admission, and parental/guardian projection of future QoL of their newborn. The last part of the questionnaire collects demographic data. We hypothesize that the maternity period is experienced more positive if mother and child go home quickly, because of less hinder to take care of their child (for example, earlier initiation of breastfeeding), and less stress (for example, emotionally or financially). The questionnaire is designed in close collaboration with Care4Neo. Care4Neo (formerly Association of Parents of Incubator Children) represents the interests of parents/guardians whose child is admitted to a hospital immediately after birth.

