### 7.2 AEs and SAEs

All (serious) adverse events reported spontaneously by the parent(s)/guardian(s) of the subject or observed by the investigator, or his staff will be recorded up until and including day 14 after birth. This period is consistent with the follow-up time and reasonably includes complications that may be linked to initial EOS management, such as a different course of EOS or readmission. In the unusual case that a newborn still receives antibiotic therapy after day 14 of life because of EOS (or a SAE), (serious) adverse events will be reported until the end of therapy.

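### After discharge, safety events are captured passively and the day-14 answers on readmission are not used to complete them; separately, return information is written for one arm only

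*Protocol*

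**What the plan says.** **What the composite counts.** Protocol 6.1.1 counts any form of respiratory support in the first week, a fluid bolus for sepsis-related instability, NICU referral for sepsis, and a pathogen-positive blood or CSF culture taken within 72 hours of birth.

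**How events are found.** Section 7.2 states: "All (serious) adverse events reported spontaneously by the parent(s)/guardian(s) of the subject or observed by the investigator, or his staff will be recorded", up to and including day 14. Section 6.3 has separate paragraphs for untreated and treated newborns. For untreated newborns it says: "Data on readmission for suspected or proven EOS will be collected". Daily recording of respiratory support and fluids, limited to the admission, stands in the paragraph on treated newborns.

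**What families are asked.** All families receive a questionnaire on day 14. Section 6.1.2 says of it: "The first part collects information on medical factors after hospitalization (side effects, number of medical visits, readmission, and medication use"). Section 8.2.1 treats it as quality of life with largely descriptive reporting. Section 10.1 says the answers go straight into Castor EDC, the system that holds the eCRF.

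**What is written about discharge.** In Section 3 the control-arm description ends with the statement that "parents/guardians receive information when to contact the hospital in case of signs of infection within the first 14 days of life". The calculator-arm description has no such statement and ends: "Discontinuation of antibiotics and discharge is at the discretion of the treating physician". The Equality paragraph of the same section gives as its aim that the "control group and the intervention group are equally recruited and monitored".

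**The concern.** The composite runs well beyond the period in which newborns are certain to be under observation. Past that point, the stated capture depends on a parent volunteering an event, on staff happening to see it, or, for untreated newborns, on a readmission being classed as EOS-related. A newborn readmitted under another label, or to a different hospital, who then receives oxygen meets the respiratory component, but no stated procedure reliably brings that event into the eCRF.

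This bears on the purpose of the trial. Section 1 justifies it by the lack of studies that account for delayed treatment, and Section 7.2 justifies the 14-day window by a changed course of EOS and by readmission. The one instrument that asks every family about readmission is not connected to either use.

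The second matter is one of consistency. One arm's description includes information at discharge and the other's is silent, under a general statement of equal monitoring.

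**Working it through.** The protocol gives no figure on this point to reproduce, so the check sets its sections side by side.

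**1. Counting window against minimum observation.** Inputs: 72 hours for proven EOS and 7 days (168 hours) for respiratory support (6.1.1); minimum observation of 12 hours for controls and 24 hours for the calculator arm (9.2; Section 3 gives 12–24 hours for controls).

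| Component | Window | After minimum observation, control (12 h) | After minimum observation, calculator (24 h) |
|---|---|---|---|
| Proven EOS | 72 h | 72 − 12 = 60 h | 72 − 24 = 48 h |
| Respiratory support | 168 h | 168 − 12 = 156 h | 168 − 24 = 144 h |

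These are hours, not shares of events. Most events may well occur early, and treated newborns stay longer. The table shows only that in both arms part of the counting window can fall after discharge.

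**2. Which route covers which late event.**

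| Late event | Stated route |
|---|---|
| EOS-related readmission, no earlier antibiotics | Named in 6.3; source and hospital not stated |
| Antibiotics for symptoms starting at 24–72 h | Secondary endpoint (6.1.2) |
| Respiratory support or fluid bolus at a readmission given another reason | Spontaneous report or staff observation only (7.2) |
| Readmission to another hospital | Not addressed, apart from NICU referral (6.3) |
| Any readmission or visit recalled by parents on day 14 | Asked (6.1.2) and stored (10.1); no safety or endpoint use stated |

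**3. The SAE route does not close the gap.** Section 7.2.2 exempts from the hospitalization criterion a newborn who starts antibiotics for EOS after discharge but within 72 hours. Such a readmission need not appear among the SAEs even when known, so composite completeness cannot rest on SAE reporting.

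**4. Scale.** At the planned 10% event rate and 820 analysed per arm (1640 / 2), 0.10 × 820 = 82 events per arm are expected. Each 10% of events missed would be about 8 per arm. The 10% missed is an assumption; the protocol gives no basis for it.

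If the same share were missed in both arms, rates of 15% and 10% would be seen as 13.5% and 9.0%. The ratio stays at 13.5 / 9.0 = 1.5, while the difference falls from 5.0 to 4.5 points. On the relative-risk criterion of 8.1, equal loss mainly costs precision.

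**The case against.** **Capture is not purely passive.** EOS-related readmissions are collected for untreated newborns, antibiotic starts for symptoms at 24–72 hours are a secondary endpoint, and consent covers electronic medical records (9.2). This stands, and it rules out saying that late harm is found only when parents come back or speak up. It leaves uncovered respiratory support or fluids given at a readmission not classed as EOS, and care in another hospital.

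**Silence is not exclusion.** Questionnaire answers reach Castor EDC, staff reading them might count as observing an event, and routing could sit in an operational document that is not shown. This stands too: the protocol does not say that the answers are kept out of safety review. But it defines how both (S)AEs and the questionnaire are handled, and connects them nowhere.

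**The stronger reading.** A reader might infer that calculator-arm parents receive less return information, that late events are missed more often there, and that non-inferiority is therefore favoured. The documents do not support this:

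- The calculator description does not say that such information is withheld; the patient information form is not shown; and Section 3 states equal monitoring.
- That arm has the longer minimum observation, which points the other way.
- Later presentation could also mean sicker newborns and more recorded composite events.

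One-sided loss would matter if it occurred. Assume 820 per arm, a design effect of 1 + (164 − 1) × 0.0025 = 1.4075, a fully ascertained control rate of 10%, and a true calculator rate of 15%. Missing 10% of calculator-arm events would then raise the chance of a false non-inferiority claim from 2.5% to 9.5% on the relative-risk margin of 1.5, or to 12.2% on the 5-point margin. The missed share and the complete control ascertainment are assumptions from outside the protocol, so this shows sensitivity and is not evidence of bias.

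**Conclusion.** The point holds as a gap in ascertainment that can affect either arm. Part of the composite's window lies after discharge, the stated capture there is incomplete, and data already requested from every family are given no role in completing it. This rests on reading 6.3 and 7.2 as written. If the daily recording is meant for all newborns and all readmissions, the gap is smaller, but the text does not say so.

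The size is unknown: neither the share of events after discharge nor the share missed is given. The hours in the table bound the exposure in time only.

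The discharge-information point is an inconsistency between parts of Section 3 and needs reconciling. It does not establish unequal care, greater under-detection in the calculator arm, or a direction of bias. Overall this is an inexpensive improvement to the completeness of a co-primary outcome, not a flaw that invalidates the comparison.

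**What to change.** 1. In 6.3 and 7.2, state that any readmission or medical visit for illness reported in the day-14 questionnaire is checked against the medical record, in both arms and whether or not antibiotics were given. It is then entered as an (S)AE where it qualifies under 7.2.2, whose 72-hour exemption stays as it is, and used to complete the co-primary composite before the record closes, at most 28 days after birth (10.5).
2. Reconcile the control description, the calculator description and the Equality paragraph in Section 3 on discharge information. Which practice applies is for the sponsor and investigators to state.

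**Cost.** Wording in three sections, an alert on existing questionnaire items, and probably few record checks, with no new contact or procedure for families. The check works only for families who respond, so response should be reported by arm. The sponsor should also confirm that the consent given covers records held at another hospital.
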